### Safety assurance

After every 5 recurrences in electively irradiated lymph nodes, an interim analysis will be performed following the ‘group sequential approach’ comparing the recurrence rate in the two treatment arms [33]. The *p*-value for the log-rank test statistic will be compared to a nominal α of 0.042 at each interim analysis (i.e. critical value of 1.728) to ensure an overall one-sided α of 0.10 [33]. For this calculation, it is assumed that accrual of 300 patients takes 4 years and that the vast majority of recurrences will be detected within 24 months.

A safety committee will be installed to undertake interim review of the trial safety. The safety committee will consist of an independent statistician and two experienced radiation oncologists in the field of head and neck cancer and will recommend on (dis)continuation of the trial.

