### Study design

This is a multicenter, phase III, single-blinded, randomized controlled trial.

Treatment allocation at randomization will be at a ratio of 2:1 in favor of the intervention arm. Randomization will be balanced for institution, tumor-site, T- and N-stage, and human papillomavirus status using minimization with a random element. Randomization and clinical trial data management is provided by the IKNL clinical research department.

A flow chart giving an overview of the study design is shown in Fig. 1.

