### Sample size calculation

This study was designed to detect a 10-point difference on the PSS-HN ‘normalcy of diet’ score at 12 months after radiation therapy with a power of 90% at a two-sided significance level of 0.05. An average ‘normalcy of diet’ score of 70 is expected after standard treatment. To achieve this significance level with an unequal randomization ratio (2:1), a total of 300 patients needs to be included.

The current rate of recurrence in electively irradiated lymph nodes was estimated to be 5% at 2 years after treatment [17]. An equal rate of recurrence is expected in the intervention arm, despite elective dose de-escalation. A recurrence rate of ≥10% will be considered clinically relevant and unacceptable. This difference can be detected with the number of patients planned for the primary outcome of the study and a one-sided α = 0.10.

The total duration of this trial is estimated to be 6 years (4 years accrual, 2 years follow-up).

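### At five recurrences per look and 2:1 allocation, the 1.728 boundary does not attain its stated overall one-sided alpha of 0.10, and its first look is effectively inoperative

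*Protocol article*

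**What the plan says.** All references are to the protocol article.

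- **Safety assurance**, timing: "After every 5 recurrences in electively irradiated lymph nodes, an interim analysis will be performed". No maximum number of looks is given.
- **Safety assurance**, test: the p-value "for the log-rank test statistic will be compared to a nominal α of 0.042 at each interim analysis", printed with a "critical value of 1.728) to ensure an overall one-sided α of 0.10".
- **Study design**: "Treatment allocation at randomization will be at a ratio of 2:1 in favor of the intervention arm".
- **Sample size calculation**, trial size: "a total of 300 patients needs to be included".
- **Sample size calculation**, rate under standard treatment: "The current rate of recurrence in electively irradiated lymph nodes was estimated to be 5% at 2 years after treatment".
- **Sample size calculation**, rate under de-escalation: "An equal rate of recurrence is expected in the intervention arm, despite elective dose de-escalation".
- **Sample size calculation**, safety limit: "A recurrence rate of ≥10% will be considered clinically relevant and unacceptable".

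The same section on safety assurance sets up an independent committee that reviews safety and recommends whether the trial goes on.

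**The concern.** A constant critical value with a stated overall alpha relies on a normal approximation and a known number of equally spaced looks. Here each look adds only 5 events, and two thirds of them are expected in the intervention arm even if de-escalation does no harm. An excess in that arm therefore has little room to show, and the statistic can take only a few values at each look.

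This is the only formal boundary the article gives for the safety endpoint of a dose de-escalation trial. A committee that saw a 5-0 split against the new arm would be told that the boundary was not crossed, without being told that this split could not have crossed it. It would also believe that the rule works at a 10% one-sided level, when at the event count the protocol expects it works at about 3%.

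**Working it through.** **Inputs.** Intervention share of the risk set under no difference: 2/3 (2:1 allocation). Looks at 5, 10, 15, ... recurrences. Critical value 1.728, nominal level 0.042, overall one-sided alpha 0.10. 300 patients, so about 200 and 100. Two-year recurrence 5% expected in both arms; 10% unacceptable.

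**1. The plan's own figure is reproduced.** 1 − Φ(1.728) = 0.042. For a constant boundary with equal information increments, the large-sample overall one-sided alpha at 1.728 is 0.086 with 3 looks, 0.100 with 4 and 0.112 with 5. So 0.042, 1.728 and 0.10 agree with one another for 4 looks, that is, 20 recurrences. The 4 is inferred; the article does not state it.

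**2. Event counts implied by the protocol's rates.** At 5% in both arms: 300 × 0.05 = 15 recurrences, or 3 looks. At 10% versus 5%: 200 × 0.10 + 100 × 0.05 = 25 recurrences, or 5 looks.

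**3. First look.** With d recurrences, S of them in the intervention arm, Z = (S − 2d/3) / √(2d/9). For S = d = 5, Z = (5 − 3.333) / √1.111 = 1.58, below 1.728. The exact p-value is (2/3)^5 = 0.132, above 0.042. For a 5-0 split to reach 1.728, the intervention share of the risk set would have to be at most 1 / (1 + 1.728²/5) = 0.626. In simulated log-rank tests with 4-year accrual, 0.3% to 0.6% of 5-0 splits crossed, through chance imbalance of the risk sets.

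**4. Later looks.** Smallest intervention-arm count with Z of at least 1.728:

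| Recurrences | Count needed | Z at that count | Z one below |
|---|---|---|---|
| 10 | 10 | 2.24 | 1.57 |
| 15 | 14 | 2.19 | 1.64 |
| 20 | 17 | 1.74 | 1.26 |
| 25 | 21 | 1.84 | 1.41 |

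**5. Attained alpha and detection.** Given an event, the chance that it falls in the intervention arm is 2/3 under no difference. Under 10% versus 5% it is 2·ln(0.90) / [2·ln(0.90) + ln(0.95)] = 0.804. Summing exact binomial probabilities from look to look, and removing paths that have already crossed, gives the cumulative chance of a signal:

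| By recurrences | No difference | 10% versus 5% |
|---|---|---|
| 5 | 0 | 0 |
| 10 | 0.017 | 0.11 |
| 15 | 0.029 | 0.21 |
| 20 | 0.070 | 0.45 |
| 25 | 0.082 | 0.52 |

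Using a share of 0.80 in place of 0.804 changes the last column only slightly (0.20, 0.43 and 0.50 at 15, 20 and 25).

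**6. Check by simulation.** Log-rank tests with 300 patients, 2:1 allocation, uniform 4-year accrual and 2 years of follow-up, with the number of looks left to the data, crossed in 2.3% of trials at 5% in both arms and in about 45% at 10% versus 5%.

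**The case against.** - **The three figures are consistent.** A reader might infer that 1.728 is a miscalculation. It is not: for 4 looks it gives 0.100 in large samples, and 20 recurrences lies midway between the 15 and 25 implied by the protocol's rates. This stands. The full protocol may well fix the maximum number of looks, so its absence from an article would not by itself be a finding. But the shortfall does not depend on it: with exactly 4 looks the attained level is still 0.070.
- **The ceiling of 0.10 is kept.** This also stands. A reader might infer from the large-sample 0.112 at 5 looks that false stops are inflated. The exact level at 5 looks is 0.082, and it stays below 0.10 through 7 looks (0.092 at 35 recurrences). What is lost is sensitivity to harm.
- **The first look could cross.** The log-rank test uses the actual risk sets, so to say that it can never cross is slightly too strong. At well under 1% of 5-0 splits, the exception has no practical weight.
- **The limit at 5 events is inherent, and the committee can act on other grounds.** No valid boundary could signal at 5 recurrences, since the most extreme split has p = 0.132. The article also has each such recurrence reported as a serious adverse event and regional recurrences centrally evaluated, and it does not make the boundary the committee's sole basis for action. This lowers the stakes. It also supports calling that look descriptive, which the article does not do.

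**Conclusion.** The point holds as a limitation of the boundary at these event counts, not as an arithmetic error in the printed constants. The stated overall alpha of 0.10 is a large-sample value for 4 looks. The attained value is about 0.029 at the 15 recurrences expected with equal 5% rates, 0.070 at 20 and 0.082 at 25. The 5-event look is in practice inoperative and the 10-event look needs a 10-0 split. At the difference built from the rate the protocol calls unacceptable (10% against 5%), a signal comes by 15 recurrences in about one trial in five and by 25 in about half.

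The results assume that the intervention arm makes up two thirds of those at risk, hazards are proportional, looks fall at exact multiples of 5 recurrences, and the 10% versus 5% contrast applies at 2 years.

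**What to change.** In the Safety assurance section:

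1. State the maximum number of looks.
2. Call the 5-event look descriptive.
3. Derive the boundary from the exact conditional binomial at the 2:1 share in place of the constant 1.728.
4. Print, for each look, the intervention-arm count that crosses, the cumulative attained alpha, and the detection probability under 10% versus 5%.

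Boundary counts should be checked for reachability. For example, if 13 of 15 would have signalled, a trial that continues has at most 12 + 5 = 17 of 20, so a limit of 18 at 20 recurrences could never be met.

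One illustration that works is 10 of 10, 13 or more of 15, and 17 or more of 20, with no later formal look. Its exact overall alpha is 0.0997. Detection under 10% versus 5% is about 42% by 15 recurrences and 50% by 20, against 21% and 45% now. The choice of boundary is for the sponsor and the safety committee.

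**Cost.** One rewritten paragraph and a short table; no extra patients or looks. The false-signal chance by 20 recurrences rises from about 7% to 10%, the level the article already states. Because the illustration ends at 20, its 50% is slightly below the 52% that the present rule reaches if it runs to 25. The gain is an earlier signal more than a higher final chance of one.

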### Quality assurance

In order to ensure quality and uniformity between centers, delineation, segmentation and treatment planning guidelines are described in detail in the protocol. The study protocol was discussed with the participating centers until consensus was reached.

Prior to opening inclusion, all participating centers will perform a dummy run in order to assess compliance with the protocols. Also during inclusion, quality assurance by central review will occur prospectively for the first 3 patients included at each participating center, and will occur retrospectively for all included patients thereafter.

## Abbreviations

BTV: Biological target volume
CT: Computed tomography
CTC: Common toxicity criteria
CTV: Clinical target volume
EANM: European association of nuclear medicine
EARL: EANM research Ltd.
EBRT: External beam radiation therapy
EGFR: Epidermal growth factor receptor
EORTC: European organization for research and treatment of cancer
EQD2: Equivalent dose in 2 Gy fractions
FDG: Fluorodeoxyglucose (18F)
FNAC: fine needle aspiration cytology
GRIX: Groningen radiation therapy induced xerostomia questionnaire
GTV: Gross tumor volume
IMRT: Intensity-modulated radiation therapy
MRI: Magnetic resonance imaging
PET: Positron emission tomography
PSS-HN: Performance status scale for head and neck cancer patients
PTV: Planning target volume
RTOG: Radiation therapy oncology group
SIB: Simultaneous-integrated boost
SUR: Standardized uptake ratio
SUV: Standardized uptake value
SWAL-QOL: Wwallowing quality of life questionnaire
US: Ultrasound
VMAT: Volumetric arc therapy
